### Bioefficacy studies and chemical analysis with cohort 2 nets

Nets belonging to cohort 2 will be randomly selected per arm for bioefficacy studies and chemical analysis. Nets of each type (Interceptor^®^ G2, Royal Guard^®^ and Interceptor^®^) will be destructively sampled from households at 6, 12, 18-, 24-, 30- and 36-months post-distribution and replaced with new nets of the same type at each sampling point. They will be subjected to laboratory bioassays (WHO cone bioassays and tunnel tests where necessary) and experimental hut trials to monitor entomological efficacy against mosquito vectors and to chemical analysis to monitor changes alphacypermethrin, chlorfenapyr and pyriproxyfen content. For laboratory bioassays, net pieces measuring 30cmx30cm will be cut from each net following WHO guidelines [13]. Nets withdrawn at annual time points (12, 24 and 36 months) will be tested in experimental huts before laboratory bioassays. The number of whole ITNs of each type to be subjected to each type of study at each timepoint is summarized in Table 1 below.

**Table 1 Tab1:** Number of Interceptor^®^ G2, Royal Guard^®^ and Interceptor^®^ ITNs to be sampled from Cohort 2 at each timepoint

Months post ITN distribution	No of ITNs to withdrawn for bioefficacy studies	No. of ITN to test in hut trials	No. of ITNs to test in lab bioassays	No. of pieces per ITN	Total number of pieces for bioassays	No. of pieces for chemical analysis^b^	ITNs sampled for other studies^c^	
0	30	–	30	5	150	150		
6	30	–	30	4	120	–		
12	54^a^	54^a^	30	4	120	120	80	
18	30	-	30	4	120	-		
24	54^a^	54^a^	30	4	120	120	80	
30	30	–	30	4	120	–		
36	54^a^	54^a^	50	4	200	200	80	
Total	282				950	590	240	

^a^These nets will be tested in hut trials prior to laboratory bioassays and chemical analysis. Hut trials will only be performed with nets withdrawn at 12, 24 and 36 months

^b^Net pieces preserved for chemical analysis will be obtained from adjacent positions on the same ITNs cut for bioassays

^c^These nets will be samples from cohort 2 nets but will be used in other studies

#### Laboratory bioassays and strain selection

Cone bioassays and tunnel tests will be performed at the CREC-LSHTM GLP-certified facility to monitor the bioefficacy of each active ingredient in each ITN brand using ITN pieces obtained from field collected nets at each time point. Current WHO ITN durability guidelines were tailored towards pyrethroid-only nets and therefore do not describe methods for assessing the bioefficacy of non-pyrethroid chemicals on ITNs [13]. Unlike pyrethroids that require a pyrethroid-susceptible *Anopheles* strain for durability bioassays, evaluation of the insecticidal activity of chlorfenapyr in Interceptor^®^ G2 and pyriproxyfen in Royal Guard® will require the use of a pyrethroid-resistant strains that is susceptible to these insecticides to reduce any confounding effects from the pyrethroid component.

Following a series of preliminary laboratory bioassays, the pyrethroid resistant *An. coluzzii* Akron strain (BEI resources) maintained at the CREC-LSHTM insectary since 2018 was identified as a suitable strain for monitoring the bioefficacy of chlorfenapyr and pyriproxyfen in Interceptor^®^ G2 and Royal Guard^®^ ITNs from the trial. Preliminary WHO susceptibility bottle bioassays [28, 29] performed with alpha-cypermethrin (12.5μg), chlorfenapyr (100μg) and pyriproxyfen (100μg) showed that the strain was resistant to pyrethroids but susceptible to chlorfenapyr and pyriproxyfen (Fig. 3). Mortality with deltamethrin in WHO tube assays increased from 19 to 77% demonstrating the partial involvement of mixed function oxidases in pyrethroid resistance in the Akron strain. Dissection of ovaries of blood-fed *An. coluzzii* Akron mosquitoes exposed to pyriproxyfen treated bottles revealed a 98% reduction in mosquito fertility relative to unexposed mosquitoes thus showing susceptibility to pyriproxyfen. The WHO cone bioassays performed with Akron mosquitoes using unwashed and washed pieces of the pyrethroid-only ITN (Interceptor^®^) showed high survival (> 60%) demonstrating that the impact of chlorfenapyr and pyriproxyfen in Interceptor^®^ G2 and Royal Guard^®^ will be less confounded by the alphacypermethrin component in these nets when tested in laboratory bioassays using this strain.

**Fig. 3 Fig3:**
[figure not shown]
Susceptibility of the pyrethroid-resistant *Anopheles coluzzii* Akron strain to insecticides in study nets. Chlorfenapyr, pyriproxyfen and alpha-cypermethrin exposures were performed in WHO bottle bioassays while deltamethrin exposures were performed in WHO filter paper tube tests. Approximately 100 mosquitoes of each strain were exposed for 1 h to each insecticide in replicates of 25. For pyriproxyfen, mosquitoes were blood-fed before exposure and their ovaries dissected after 72 h to assess ovary development

Based on results from these preliminary bioassays, the testing plan in Table 2 will be used in laboratory bioassays for monitoring the bioefficacy of each active ingredient in the different ITN brands in the trial. In line with WHO guidelines, ITN bioefficacy at each timepoint will be expressed in terms of the proportion of ITNs passing the efficacy criteria for each active ingredient in cone bioassays or tunnel tests.

**Table 2 Tab2:** Summary of laboratory bioassay methodology and outcome measures for assessing the insecticidal durability of Interceptor^®^ G2 and Royal Guard^®^ in Benin compared to Interceptor^®^

ITN type	Brand name	Active ingredient	Mosquito strain	Mosquito age and status (N)	Primary test method (exposure time)	Key outcome measures	ITN efficacy criteria	Remarks/additional tests
Pyrethroid-only	Interceptor	alpha-cypermethrin	Susceptible *An. gambiae* s.s. Kisumu	unfed, 3–5 days old (40–50/net)	cone bioassays (3 min)	Knockdown, 24 h Mortality	knock-down ≥ 95% or mortality ≥ 80%	Tunnels for failed nets
Pyrethroid-chlorfenapyr	Interceptor G2^a^	alpha-cypermethrin	not tested	not tested	not tested	not tested	not tested	not tested due to lower dose of pyrethroid
		chlorfenapyr	Pyrethroid-resistant *An. coluzzii* Akron	unfed, 5–8 days old (100/net)	Tunnel tests (overnight)	72 h Mortality and Blood-feeding inhibition	Mortality ≥ 80% or Blood-feeding inhibition ≥ 80%	1 net piece per ITN
Pyrethroid- pyriproxyfen	Royal Guard	alpha-cypermethrin	Susceptible *An. gambiae* s.s. Kisumu	unfed, 5–8 days old (40–50/net)	cone bioassays (3 min)	Knockdown, Mortality	knock-down ≥ 95% or mortality ≥ 80%	Tunnels for failed nets
		pyriproxyfen	Pyrethroid-resistant *An. coluzzii* Akron	blood-fed, 5–8 days old (80–100/net)	cone bioassays (3 min) plus ovary dissection after 72 h	% reduction in fertility relative to control^b^	Reduction in fertility relative control	> 30% fertility required in control

^a^For Interceptor G2, given the low dose of alpha-cypermethrin, chlorfenapyr bioefficacy will be prioritised

^b^Mosquitoes presenting with Christopher stage V ovaries, will be considered fertile

Alpha-cypermethrin bioefficacy in Royal Guard^®^ and Interceptor^®^ will be assessed using the susceptible *An. gambiae* Kisumu strain in 3 min cone bioassays following current WHO protocols. At each timepoint, 40–50 unfed 3–5 days old *An. gambiae* Kisumu mosquitoes will be exposed to each whole Royal Guard^®^ and Interceptor^®^ ITN in replicates of 5 mosquitoes per cone and 2 cones per ITN piece. ITNs which fail to achieve WHO efficacy criteria in these cone bioassays (pooled knock-down ≥ 95% or pooled 24h mortality ≥ 80%) will be subjected to tunnel tests. For each ITN that failed in cone bioassays, only one ITN piece (with cone bioassay mortality that is closest to the mean) will be tested in tunnels. Approximately 100 unfed 5–8 days old susceptible *An gambiae* Kisumu will be exposed to each ITN piece in the tunnel tests and efficacy of alpha-cypermethrin in Interceptor^®^ and Royal Guard^®^ will be measured in terms of mortality after 24h (≥ 80%) or blood-feeding inhibition (≥ 90%).

Given the relatively low concentration of alpha-cypermethrin in Interceptor^®^ G2 (100 mg/m^2^), bioefficacy studies performed with the net will focus more on its chlorfenapyr component. The unsuitability of cone bioassays for assessing the efficacy of chlorfenapyr on ITNs has been demonstrated in several studies [19, 30] hence only tunnel tests will be used for evaluating the activity of chlorfenapyr in Interceptor^®^ G2 with the pyrethroid-resistant Akron strain. To improve the efficiency of the tunnel test bioassays, only 1 ITN piece per whole Interceptor^®^ G2 will be tested in tunnels. A total of ~ 100 unfed 5–8 days old pyrethroid resistant *An coluzzii* Akron will be exposed overnight in each tunnel test with Interceptor^®^ G2 and efficacy in tunnels will be measured in terms of mosquito mortality after 72h (≥ 80%) or blood-feeding inhibition (≥ 90%).

For bioefficacy of pyriproxyfen in Royal Guard^®^, blood-fed 5–8 days old mosquitoes of the pyrethroid-resistant *An coluzzii* Akron strain will be exposed for 3 min in cone bioassays and assessed for the impact on ovary development using dissection. Dissections will be performed under microscope by trained technicians, 72h after exposure. Mosquitoes presenting with Christopher stage V ovaries will be classified as fertile (Fig. 4) [31] and the proportional reduction in fertility relative to control unexposed mosquitoes at each bioassay will be determined for each ITN. A total of 80–100 blood-fed mosquitoes will be tested against each Royal Guard^®^ ITN in replicates of 5 mosquitoes per cone and 4 cones per ITN piece. As there are currently no WHO defined cut-offs for the reproductive effect of PPF-treated ITNs in bioassays, the pass rate of Royal Guard® nets at each timepoint will be assessed based on their capacity to reduce the fertility of exposed mosquitoes relative to the untreated control. Only tests for which at least 30% of unexposed mosquitoes are found fertile will be considered valid. Efficacy in these cone bioassays will be considered the final endpoints for performance of pyriproxyfen in Royal Guard^®^; no further tests will be performed in tunnels with failed nets.

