Current WHO ITN evaluation guidelines define specific thresholds for determining the efficacy of ITNs in insecticidal durability bioassays. Nets that induce ≥ 95% knockdown and/or ≥ 80% mortality in cone bioassays or ≥ 80% mortality and/or ≥ 90% blood feeding inhibition in tunnel tests are considered efficacious. While proposing these same efficacy criteria for the laboratory bioassays for alpha-cypermethrin and chlorfenapyr bioefficacy in the study nets, it is recognized that these cut-offs were primarily developed for fast-acting pyrethroid insecticides on nets and may need to be modified for non-pyrethroid insecticides. Indeed, new draft WHO guidelines proposed for ITN prequalification aim more for a weight of evidence approach and do not allude to specific efficacy thresholds [39]. The weight of evidence approach may be suitable for assessing individual ITN products but could be challenging for comparing between ITN product brands and making programmatic and procurement decisions, which is usually the main objective for ITN durability studies. Efficacy criteria for the sterilizing effects of pyriproxyfen on ITNs are yet to be defined in WHO guidelines. Further studies investigating correlations between the sterilizing effects of Royal Guard^®^ nets in laboratory bioassays and their epidemiological performance against clinical malaria in the current trial, may contribute towards the identification of a suitable cut-off for the impact of pyriproxyfen in ITN durability studies.

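### Table 2 sets the chlorfenapyr tunnel-test limit for blood-feeding inhibition at 80%, but the Methods text and Discussion set it at 90%; the choice matters only for nets with mortality below 80% and inhibition between the two limits

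*Protocol article*

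**What the plan says.** All of the following is in the protocol article.

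- **Methods, Laboratory bioassays and strain selection, Table 2.** In the chlorfenapyr row for Interceptor G2 (Akron strain, overnight tunnel test, 72 h mortality), the efficacy criterion is "Mortality ≥ 80% or Blood-feeding inhibition ≥ 80" per cent. The table is presented as operative: "the testing plan in Table 2 will be used in laboratory bioassays for monitoring the bioefficacy of each active ingredient".
- **Same section, text after Table 2.** For the same net, strain, test and number of mosquitoes: "efficacy in tunnels will be measured in terms of mosquito mortality after 72h (≥ 80%) or blood-feeding inhibition (≥ 90" per cent). This text also uses 90% inhibition for Interceptor and Royal Guard nets that fail the cone test and are retested in tunnels.
- **Discussion.** The WHO tunnel criteria are reported as "≥ 80% mortality and/or ≥ 90% blood feeding inhibition in tunnel tests are considered efficacious", and the authors adopt them for both insecticides: "While proposing these same efficacy criteria for the laboratory bioassays for alpha-cypermethrin and chlorfenapyr bioefficacy in the study nets".
- **Use of the rule.** The section introducing Table 2 makes the proportion of nets passing the bioefficacy result at each time point. The Statistical analysis section applies a chi-squared test to the proportion meeting WHO criteria.

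**The concern.** One pass/fail limit has two values, and no passage explains a separate 80% inhibition limit for chlorfenapyr. Someone scoring from the table and someone scoring from the text can classify the same net differently.

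For Interceptor G2 the tunnel test is the only laboratory bioassay, done on one piece per net, so no second test corrects a classification. If the table were followed, Interceptor G2 would face an inhibition limit of 80% in tunnels while the other two products face 90%. The Discussion ties durability results to product comparison and procurement, and the Conclusion offers the methods as input to standard guidelines, so the table may also be copied by others.

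**Working it through.** The article states no pass rate, power or sample size for this criterion, so there is no figure of its own to reproduce. The check has two parts.

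**1. Where the two rules differ.** Let M be observed 72 h mortality and I observed blood-feeding inhibition.

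- Table 2: pass if M ≥ 80% or I ≥ 80%.
- Text and Discussion: pass if M ≥ 80% or I ≥ 90%.

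Any net with M ≥ 80% passes both. Any net with I ≥ 90% passes both. A net with M < 80% and I < 80% fails both. The rules disagree only when M < 80% and 80% ≤ I < 90%.

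**2. How many nets could be affected.**

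Inputs from the article: about 100 mosquitoes per Interceptor G2 net (Table 2, "unfed, 5–8 days old (100/net")); 30 nets per type and time point (Statistical analysis; Table 1 lists 50 at month 36).

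Inputs assumed, because the article does not give them: 100 mosquitoes in the control tunnel; control feeding c of 60% to 80%; true inhibition B; true mortality m; mortality and feeding independent; all nets alike.

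Formulas:

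- Control fed ~ Bin(100, c); treated fed ~ Bin(100, c(1 − B)); I = 1 − treated fed / control fed.
- P_I(t) = P(I ≥ t), for t = 0.80 or 0.90.
- P_M = P(Bin(100, m) ≥ 80).
- P(pass) = 1 − (1 − P_M)(1 − P_I(t)).

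Feeding route at B = 0.85, by exact enumeration:

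- c = 0.60: P_I(0.80) = 0.847, P_I(0.90) = 0.155
- c = 0.80: P_I(0.80) = 0.886, P_I(0.90) = 0.111

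Mortality route: P_M = 0.016 at m = 0.70, 0.149 at 0.75, 0.559 at 0.80 and 0.999 at 0.90. At m of 0.60 or less it is practically zero.

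Example, m = 0.80 and c = 0.60:

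- 80% limit: 1 − 0.441 × 0.153 = 0.933; × 30 = 28.0 nets
- 90% limit: 1 − 0.441 × 0.845 = 0.627; × 30 = 18.8 nets

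Expected passes out of 30 at B = 0.85, over c = 0.60 to 0.80:

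| True mortality | 80% limit | 90% limit |
|---|---|---|
| 70% or less | 25.4-26.6 | 3.3-5.1 |
| 75% | 26.1-27.1 | 7.3-8.4 |
| 80% | 28.0-28.5 | 18.3-18.8 |
| 90% | 30.0 | 30.0 |

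Outside the band, with true mortality of 60% or less so that only feeding decides:

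- B = 0.70: 0.9-1.9 against 0 of 30
- B = 0.95: 30 against 28.3-29.0 of 30

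If nets vary (mean B = 0.85, control feeding fixed at 75%, feeding route only), the pass rates are 82% against 24% with a between-net SD of 0.05, and 74% against 39% with an SD of 0.10.

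**The case against.** The strongest reply is that the intended rule can be recovered. The Methods text and the Discussion agree on 90%, and the Statistical analysis section refers to the WHO criteria, which the Discussion gives as 90%. One cell is out of line, plausibly a slip repeating the 80% printed next to it. That stands as evidence for which value to keep. It does not remove the fault, because the article says the plan in that table is the one to be used.

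The second reply is that mortality may settle the matter. The Discussion expects chlorfenapyr to maintain killing as the nets age; if mortality stays well above 80%, the inhibition limit is irrelevant. This also stands, and it limits the size of the effect.

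A reader might infer three stronger things that the documents do not support:

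- *That pass rates differ greatly whichever way the nets behave.* They do so only for nets in the band identified above.
- *That Interceptor G2 results have been inflated.* The Status of study section says bioassays on nets up to 24 months are under way, but nothing shows that any net was scored at 80%.
- *That a strict like-for-like tunnel comparison is broken.* Interceptor and Royal Guard reach the tunnel only after failing the cone test, and are then tested with the Kisumu strain at 24 h; Interceptor G2 is tested with Akron at 72 h. The comparison already differed in those respects. Table 2 itself prints no tunnel limit for the other two nets.

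Nor is this an arithmetic error: nothing is miscalculated.

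**Conclusion.** The inconsistency is real, and nothing in the article expressly resolves it. It concerns a decision threshold for a reported endpoint, so it should be corrected.

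Its effect is conditional. With true inhibition near 85%, it can move the count from about 25-27 to 3-5 of 30 nets when true mortality is 70% or less, and from about 28 to 18-19 when mortality is 80%. It changes nothing at 90% mortality and little when true inhibition is 70% or less, or uniformly 95%. Net-to-net variation narrows the contrast.

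These counts rest on assumed values for mortality, inhibition and control feeding, and on independence of mortality and feeding. They show what could happen, not what did. The contradiction itself needs no assumption.

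**What to change.** Change the inhibition limit in the Table 2 chlorfenapyr cell to 90% or more, leaving the mortality limit as it is. The table then agrees with the text below it, with the Discussion, and with the tunnel limit used for the other two nets.

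State which limit was applied to Interceptor G2 nets already tested. Reclassify only those scored at 80%; only nets with mortality below 80% and inhibition from 80% to under 90% can change.

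The cost is one table cell and a check of existing scoring records. No new testing is needed. If any nets were scored at 80%, the Interceptor G2 pass rate may fall.

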## Methods

### Study arms

The study consists of three arms evaluating the durability of two dual AI ITNs (Interceptor^®^ G2 and Royal Guard^®^) compared to a standard pyrethroid-only ITN Interceptor^®^. Study nets are all blue, rectangular, and sizes of 1.8 m long, 1.8 m wide, and 1.8 m high (Interceptor^®^ and Interceptor^®^ G2) and 1.8 m long, 1.8 m wide, and 1.6 m high (Royal Guard^®^). A description of the specifications of the three ITN types is provided below:Interceptor^®^ G2 (BASF AGRO B.V.), is a WHO-prequalified 100-denier, polyester ITN coated with a mixture of alpha-cypermethrin and chlorfenapyr at target concentrations of 100 mg/m^2^ (± 25%) and 200 mg/m^2^ (± 25%), respectively. The bursting strength of the fabric is ≥ 405 kPa while the mass per unit area is 40 g/m^2^ (± 10%) for 100 denier yarn.Royal Guard^®^ (Disease Control Technologies, LLC, USA), is a WHO-prequalified 100-denier, polyethylene ITN incorporated with a mixture of alpha-cypermethrin and pyriproxyfen at target concentrations of 261 mg/m^2^ (± 25%) and 225 mg/m^2^ (± 25%) respectively. The bursting strength of the fabric is ≥ 405 kPa while the mass per unit area is 45 g/m^2^ (± 10%) for 150 denier yarn.Interceptor^®^ (BASF AGRO B.V.), is a WHO-prequalified 100-denier, polyester ITN coated with alpha-cypermethrin at target concentrations of 200 mg/m^2^ (± 25%). The bursting strength of the fabric is ≥ 405 kPa while the mass per unit area is 40 g/m^2^ (± 10%) for 100 denier yarn. Interceptor® is the control arm of the trial against which Interceptor^®^ G2 and Royal Guard® are compared.

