**Fig. 4 Fig4:**
[figure not shown]
Developmental stages of Anopheline ovaries [31]. Mosquitoes with fully developed stage V ovaries (elongated boat-shaped eggs with lateral floats) are considered fertile while mosquitoes with stage I-IV ovaries containing underdeveloped eggs are considered infertile

All bioassays will be performed at 27 ± 2 °C and 75% ± 10% relative humidity. For each ITN type, each active ingredient and each bioassay, a direct comparison will be made with a new unused net during bioassays. A new Interceptor^®^ net will be tested as positive control in bioassays evaluating pyriproxyfen in Royal Guard^®^ and chlorfenapyr in Interceptor^®^ G2. Prior to each bioassay round, susceptibility tests will be performed to monitor the suitability of the *An coluzzii* Akron strain. While efforts will be made to test nets withdrawn at all timepoints (every 6 months) in laboratory bioassays, given the volume of bioassays required, to improve efficiency, nets withdrawn at 0, 6, 12, 24 and 36 months post-ITN distribution will be prioritized over other timepoints.

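### The chlorfenapyr pass rule for Interceptor G2 accepts blood-feeding inhibition alone, an endpoint not specific to chlorfenapyr on a net that also carries alpha-cypermethrin

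*Protocol article*

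**What the plan says.** The point concerns Methods, Laboratory bioassays and strain selection, with its Table 2.

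- **Pass rule in the text.** For Interceptor G2 against the pyrethroid-resistant Akron strain, "efficacy in tunnels will be measured in terms of mosquito mortality after 72h (≥ 80%) or blood-feeding inhibition (≥ 90" per cent).
- **Pass rule in Table 2.** The chlorfenapyr row is also an either-or rule, with a different inhibition cut-off: "Mortality ≥ 80% or Blood-feeding inhibition ≥ 80" per cent.
- **The same endpoint for the pyrethroid.** Alpha-cypermethrin efficacy of Interceptor and Royal Guard in tunnels "will be measured in terms of mortality after 24h (≥ 80%) or blood-feeding inhibition (≥ 90" per cent). That test uses the susceptible Kisumu strain.
- **What is on the net.** Study arms describes Interceptor G2 as "coated with a mixture of alpha-cypermethrin and chlorfenapyr at target concentrations of 100 mg/m^2^ (± 25%) and 200 mg/m^2^ (± 25" per cent). Its alpha-cypermethrin row in Table 2 reads "not tested due to lower dose of pyrethroid".
- **Evidence on the strain.** With unwashed and washed pieces of Interceptor in cone tests, Akron "showed high survival (> 60" per cent).
- **Comparator.** "A new Interceptor^®^ net will be tested as positive control in bioassays evaluating pyriproxyfen in Royal Guard^®^ and chlorfenapyr in Interceptor^®^ G2". No pass criterion refers to its result.
- **Use of the result.** Statistical analysis applies a chi-squared test to the proportion of nets passing for each active ingredient.
- **The authors' caveat.** The Discussion says that "these cut-offs were primarily developed for fast-acting pyrethroid insecticides on nets" and may need changing for other insecticides.

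**The concern.** Table 2 labels the Interceptor G2 tunnel test as the chlorfenapyr assay, and objective 2 concerns insecticidal activity over three years. The Discussion says the strain must allow the non-pyrethroid to be assessed without interference from the pyrethroid, and it credits chlorfenapyr with maintaining the killing effect as nets age. The Background describes chlorfenapyr as slowly inducing death. The mortality half of the rule fits that mode of action. The inhibition half need not: a mosquito kept from feeding may have been kept off by either ingredient, and nothing in the rule says which.

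For pyriproxyfen the plan chose an endpoint tied to the mechanism, ovary development. For chlorfenapyr it kept the general either-or rule.

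At stake is the meaning of the headline bioassay result. If enough pyrethroid-driven inhibition persists, the Interceptor G2 chlorfenapyr pass proportion could hold up at 24 or 36 months while chlorfenapyr activity falls.

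**Working it through.** The protocol gives no error rate or power for this rule, so there is no figure to reproduce. The check asks how often a net with no chlorfenapyr activity would pass.

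**Inputs from the protocol**
- About 100 mosquitoes per tunnel and one piece per net (Table 2 and text).
- Mortality cut-off 80%; inhibition cut-off 90% (text) or 80% (Table 2).
- Akron survival above 60% with Interceptor in cones, so mortality below 40%.
- Nets in laboratory bioassays per time point: 30, and 50 at month 36 (Table 1).

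**Assumptions (not in the protocol)**
- Control feeding c between 60% and 90%.
- True pyrethroid-only inhibition b in Akron tunnels between 70% and 95%.
- 100 mosquitoes in the control tunnel, and independence between mosquitoes.

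**Mortality route.** The number dead is Binomial(100, m), and a pass needs 80 or more.
- m = 40%: P = 3.4 × 10⁻¹⁶.
- m = 60%: P = 1.6 × 10⁻⁵.
- m = 70%: P = 0.016.
- m = 75%: P = 0.149.

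If tunnel mortality from the pyrethroid alone resembled the cone figure, this route would be closed and a false pass could come only through inhibition. The last two lines show that this depends on tunnel mortality staying well below the cut-off, which the protocol does not document either.

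**Inhibition route.** Inhibition = 1 − F_t/F_c, where the number fed in the net tunnel is F_t ~ Binomial(100, c(1 − b)) and in the control tunnel F_c ~ Binomial(100, c). For example, with c = 70% and b = 90% the expected counts are 7 and 70 fed, exactly on the 90% cut-off. The pass probabilities, as the range over c = 60–90%, are:

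| True inhibition b | Pass at 90% (text) | Pass at 80% (Table 2) |
|---|---|---|
| 70% | below 0.1% | 2–6% |
| 75% | 0.4% or less | 15–22% |
| 80% | 0.7–2.8% | about 52% |
| 85% | 10–16% | 85–90% |
| 90% | about 53% | 98.6% or more |
| 95% | 94–98% | over 99% |

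Treating the control count as fixed at 70 gives 60% instead of 53% at b = 90%. Counting the control's own sampling error, as above, is the better calculation.

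**In nets.** If all 30 nets at a time point had lost chlorfenapyr activity, the expected number passing at the 90% cut-off would be 30 × 0.004 = 0.1 or fewer at b = 75% or less, 30 × 0.10 to 30 × 0.16 = 3 to 5 at b = 85%, and 30 × 0.53 = 16 at b = 90%.

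If feeding varied between tunnels more than the binomial allows, these curves would be flatter: more false passes below the cut-off and fewer above it.

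**The case against.** **Different strains.** The plan uses inhibition as an alpha-cypermethrin endpoint in susceptible Kisumu, whereas the chlorfenapyr test uses Akron, chosen for its resistance. The shared endpoint does not show that the pyrethroid inhibits feeding strongly in Akron. This stands and weakens the overlap. It does not remove it: the Methods claim only to reduce confounding, and the net-based evidence concerns killing in cones.

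**An unlikely scenario.** A false pass needs chlorfenapyr lost while the pyrethroid still gives inhibition near the cut-off. The Discussion expects the reverse, because the alpha-cypermethrin dose is about half the usual one and likely less durable. A net that has lost both would fail. This is a fair reason to expect few false passes, but the design does not test the expectation on Interceptor G2.

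**The loss would show elsewhere.** A reader might infer that loss of chlorfenapyr would go unseen. The protocol does not support that. Table 2 records 72 h tunnel mortality, chemical content is read per net at 0, 12, 24 and 36 months, and the hut trials report 72 h mortality of field nets at 12, 24 and 36 months. What stands is narrower: none of these enters the pass proportion.

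**Mortality is not specific either.** Tunnel mortality is also an alpha-cypermethrin endpoint, and cone survival is no better evidence for overnight mortality than for overnight inhibition. This stands as a limit on the remedy. Mortality is nevertheless the effect that the protocol attributes to chlorfenapyr.

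**The rule was adopted openly.** The Discussion takes over the WHO criteria knowingly and says that fixed thresholds help product comparison. With testing under way, replacing the rule would be a post hoc change. This argues for adding a result rather than removing one.

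**Conclusion.** The point holds as a limited one. Both statements of the rule let an Interceptor G2 net pass for chlorfenapyr on feeding inhibition alone, and nothing in the rule separates the contributions of the two ingredients. A net with little chlorfenapyr activity could therefore be counted as passing.

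The protocol supports only that this can happen. A reader might infer that the pass rates will in fact be inflated, but that would need pyrethroid-only inhibition in Akron tunnels, and no such figure is given. At the 90% cut-off the problem is negligible if that inhibition is 75% or less and substantial from about 85% upwards, under the assumptions of 100 mosquitoes per tunnel, 60–90% control feeding and independent mosquitoes.

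The different inhibition cut-offs in Table 2 and the text are a separate contradiction that must be reconciled. The present point holds at either value and is larger at the lower one.

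**What to change.** 1. At each time point, report the proportion of Interceptor G2 nets with 72 h tunnel mortality of at least 80% as the chlorfenapyr-specific result.
2. Report blood-feeding inhibition separately, as an outcome of the whole net.
3. Keep the either-or pass rate alongside, for comparability with studies that use the WHO rule.
4. Show mortality and inhibition for the Interceptor net run in the same Akron round. State that a new net at a 200 mg/m² target is a conservative comparator for an aged component that started at 100 mg/m²: it may overstate the pyrethroid's share and so understate that of chlorfenapyr. State also that tunnel mortality is not wholly free of pyrethroid effect.
5. Reconcile the inhibition cut-off between Table 2 and the text.

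Both outcomes are already planned for every tunnel, so the cost is wording and a few lines of analysis. The downside is that the mortality-only rate may be lower. For nets already tested it is an analysis added after testing began and should be labelled so: Status of study reports that bioassays on nets withdrawn up to 24 months are in progress.
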